### 2.9. Data collection methods

The validated Korean versions of the PSQI (30), ISI (32), and ESS (34) will be used. The PSQI is a self-rating questionnaire, and the investigators will check the answers of the participants every time to determine that they understand the question and respond properly and also to identify if a missing value or error exists. Sleep indicators extracted by PSG are also important outcomes of this trial. Qualified investigators will interpret the results of PSG. To minimize the difference among the assessors, the raw PSG data obtained at the two sites will be gathered at one site, which will take responsibility for interpreting the PSG results.

In the screening process, the PHQ-9 (26) and GAD-7 (27) will be measured to exclude participants with clinical depression or anxiety. In addition, the STOP-Bang (28) will be used to exclude participants with a high risk of obstructive sleep apnea. Validated Korean versions of the PHQ-9 (36), GAD-7 (37), and STOP-Bang (38) will be used. The investigators will send messages to participants to inform them of the dates of visits and encourage them to complete follow-ups.

### 2.10. Data management

The data obtained from the source documents, such as questionnaires, worksheets, and medical records, will be entered into an electronic Case Report Form (eCRF). Using the validation data system of eCRF, data ranges are set for each value, and a query will appear when outlier data are entered. Full Source Data Verification (SDV) for data entered into the eCRF will be conducted during routine monitoring visits. In addition, prior to trial initiation, a data management plan has already been prepared. The system query of the eCRF is planned to be checked bimonthly.

### 2.11. Statistical methods

#### 2.11.1. Definition of the population to be analyzed

The main population to be analyzed for evaluating efficacy is the Per Protocol (PP) set, and Full Analysis (FA) set will be used supplementary. The PP set will include participants who complete the trial without major deviations from the planned protocol. The FA set will include an additional population for evaluating the efficacy and will include participants who are randomized into groups and who complete more than one assessment after the administration of the investigational products. The main analysis population for evaluating safety will be the safety set, which includes participants administered the investigational products more than once. In the primary and secondary outcomes, there will be no missing data in the PP set, and missing data in the FA set will be imputed using the last observation carried forward method.

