The objective of this randomized, double-blind, placebo-controlled, parallel-group clinical trial is to evaluate the efficacy and safety of HSF extract on sleep improvement in adults with sleep discomfort and to compare them with that of placebo. Eighty participants will be randomly allocated to the HSF extract or placebo groups in a 1:1 ratio. The superiority of the HSF extract over placebo will be tested.

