### 2.5. Sample size

The primary objective of this clinical trial is to evaluate the superiority of the PSQI global score improvement in the HSF extract group compared to that in the placebo group. To estimate the mean difference of the PSQI global score between both groups and the pooled standard deviation, the results of a previous randomized trial (35) will be used to assess the PSQI global score. In the earlier trial, the mean difference of change from baseline between the two groups was −3.95 (−3.96 in the treatment group and − 0.01 in the placebo group). The standard deviation of the change from baseline was not presented, and the largest value of the standard deviation of the PSQI global score was 3.4. To calculate the sample size for this study, the mean difference and pooled standard deviation were estimated as −2.50 and 3.4, respectively. With a 5% level of significance, 80% power of the test, and 25% dropout rate, the required sample size for each group was calculated as 40.

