#### 2.11.2. Statistical method for analyzing primary and secondary outcomes

The change from the baseline PSQI global score at 4 weeks between the two groups will be compared using a two-sample *t*-test or Wilcoxon rank sum test, according to the normality of data. Additionally, changes in the PSQI global score over time in each group will be compared using a paired *t*-test. A generalized linear model (GLM) with covariates of caffeine consumption, age, body mass index, smartphone usage time, and drinking habits can also be conducted. In case of significant differences in baseline characteristics between the two groups, these baseline characteristics can be considered as covariates in conducting the GLM.

The statistical method used for analyzing secondary outcomes is identical to that used to analyze the primary outcome.

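### The superiority conclusion rests on the Per Protocol set, so the primary comparison is not protected by randomisation and could be biased in either direction

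*Protocol article*

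**What the plan says.** The Introduction gives the aim: "The superiority of the HSF extract over placebo will be tested". Section 2.5 repeats it for the PSQI global score.

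Section 2.11.1 then fixes the populations: "The main population to be analyzed for evaluating efficacy is the Per Protocol (PP) set, and Full Analysis (FA) set will be used supplementary". Membership of the PP set is defined by what happens during follow-up: "The PP set will include participants who complete the trial without major deviations from the planned protocol". By contrast, the FA set is not simply everyone randomised. It consists of "participants who are randomized into groups and who complete more than one assessment after the administration of the investigational products". On missing values, the section applies a carry-forward method to the FA set only: "there will be no missing data in the PP set, and missing data in the FA set will be imputed using the last observation carried" …

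For the primary comparison, by t-test or Wilcoxon rank sum test, Section 2.11.2 states: "The change from the baseline PSQI global score at 4 weeks between the two groups will be compared using a two-sample" … An optional generalised linear model is described, but baseline PSQI is not among its named covariates.

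No section makes the FA set primary or co-primary, and no reason is given for preferring PP.

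**The concern.** Completing the trial and avoiding major deviations are both events after randomisation. An analysis restricted to people who meet those conditions compares two selected groups, not the two groups that chance created. In a superiority trial the primary result should keep that protection, and here it is given up by a stated rule. This is not a detail left to an analysis plan.

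The article also describes ways out of the PP set that could depend on the product or on how a participant is sleeping. A participant may refuse the product (Section 2.3), mild dyspepsia is named as possible (Section 2.13), and anyone unblinded, for example after a serious adverse reaction, is dropped (Section 2.8).

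What is at stake is the main efficacy result, which is to be submitted to the Korean regulator in support of a health claim (Section 4.4).

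**Working it through.** **1. The plan's own figure.** Section 2.5 says that "the mean difference and pooled standard deviation were estimated as −2.50 and 3.4, respectively". Its stated result is 40 per group, introduced in these words: "With a 5% level of significance, 80% power of the test, and 25% dropout rate, the required sample size for each group was calculated as" … Sidedness is not stated. Taking a two-sided test:

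- n per arm = 2 × [3.4 × (1.960 + 0.842) / 2.5]² = 29.03, rounded up to 30.
- Allowing for dropout: 30 / 0.75 = 40.

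This matches. A one-sided 5% test would give 23, then 31, which does not. The design therefore aims for about 30 evaluable participants per arm. If the whole allowance is used, 40 − 30 = 10 per arm, or 20 of 80, are absent from the primary comparison.

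**2. How large could a selection bias be?** Assumptions not in the documents: no true effect, SD of change 3.4, 40 per arm, 25% excluded from each arm. Exclusion is driven by a normal score that has correlation ρ with poor response, and the highest 25% of scores are excluded. The mean shift among those retained is

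ρ × 3.4 × φ(0.674) / 0.75 = ρ × 3.4 × 0.3178 / 0.75 = ρ × 1.44 points.

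At ρ = 0.3 this is 0.43 points, and at ρ = 0.5 it is 0.72 points. If both arms have the same ρ and the same exclusion rate, the shifts cancel.

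Simulation (40,000 trials per scenario, two-sample t-test, two-sided 5%; a negative difference favours HSF):

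| Exclusion pattern | Mean difference | Type I error |
|---|---|---|
| Unrelated to outcome | about 0 | 4.9% |
| Same in both arms, ρ = 0.5 | about 0 | 4.8% |
| Poor responders leave HSF only, ρ = 0.3 | −0.43 | 7.6% |
| Poor responders leave HSF only, ρ = 0.5 | −0.72 | 13.1% |
| Reversed (ρ = −0.5 in HSF only) | +0.72 | 13.0%, nearly all against HSF |
| Same ρ = 0.5, but 25% excluded from HSF and 10% from placebo | −0.39 | 7.4% |

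The last row shows that unequal exclusion rates alone can produce bias when exclusion is related to outcome.

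**3. What moving to all randomised participants does to power** (40 per arm, t-test, two-sided 5%):

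- Full effect: 2.5 / (3.4 × √(2/40)) = 3.29; power about 90%.
- If 25% of the active arm gain nothing (assumption): the mean effect is 2.5 × 0.75 = 1.875; 1.875 / (3.4 × √(2/40)) = 2.47; power about 68%.
- Same dilution with baseline adjustment (assumed correlation 0.5 between baseline and change): SD = 3.4 × √(1 − 0.25) = 2.94; ratio 2.85; power about 80%.

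**The case against.** The strongest reply has four parts.

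- **Bias is not inevitable.** The trial is double-blind (Section 2.8). If the product does nothing, leaving because of poor sleep should be similar in both arms, and then there is no bias. This stands. The figures of 7–8% and 13% depend on assumed one-sided correlations that nothing in the documents supports or refutes.
- **There is a safeguard.** Section 4.3 provides for a blind review to confirm the analysis set before the data are locked. This limits discretionary exclusions. It does not prevent dropout caused by the product's own effects, because those participants have already gone.
- **The FA analysis is prespecified.** It is, but only as supplementary. As written it also requires more than one assessment after dosing and carries the last observation forward, so it does not supply a full intention-to-treat result.
- **The sample size already allows for losses.** That is correct, and the calculation is sound. An allowance for losses protects power, but it does nothing about bias.

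A reader might infer that PP selection generally favours the active product, or that the plan declares success when PP is positive and FA negative. The article supports neither. The direction depends on who leaves which arm, and no rule for discordant results is stated; calling PP the main set only suggests which result would take precedence. Nor does the article forecast 25% dropout, since that figure is a planning allowance, and it does not say whether the allowance also covers major deviators. A claim that power falls below plan would need an invented number of further exclusions.

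**Conclusion.** The point holds as a design fault in the choice of primary population. A superiority objective is tied to a set defined by post-randomisation events, and up to about 10 of 40 per arm may be outside it. The primary comparison can therefore be biased either way when exclusions are related to outcome and differ between arms.

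The illustrated range runs from no bias with about 5% type I error to roughly 0.7 points with 13% error. The larger value is 0.72 / 2.5 = 29% of the planned effect. These figures show how sensitive the analysis is and do not predict what will happen in this trial. The case for changing the rule rests on the lost protection of randomisation and on how little the change costs before unblinding. It does not depend on any one error rate.

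**What to change.** Amend Sections 2.11.1 and 2.11.2 before unblinding:

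- Make all randomised participants, analysed as allocated, the primary efficacy set. Base the superiority conclusion on it and keep PP as supportive.
- Remove from the FA definition the condition of more than one assessment after dosing. With that condition left in, exchanging the two labels would still exclude early dropouts.
- Replace last observation carried forward as the primary missing-data method. Options are a baseline-adjusted model valid under missing at random, or multiple imputation, with a sensitivity analysis for departures from that assumption. The text names a week-2 measurement for the ISI, ESS and sleep diary but not for the PSQI. If there is none (Figure 1 is not available here), carrying forward would set early dropouts to zero change.
- Seek the week-4 PSQI from participants who stop the product early. State how participants dropped after unblinding under Section 2.8 enter the analysis.

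The cost is a short amendment and some extra follow-up effort, with no additional participants. The real downside is possible dilution. At 40 per arm, power is about 90% with the full 2.5-point effect but about 68% by t-test if a quarter of the active arm gain nothing. It returns to about 80% only with baseline adjustment, under the assumed correlation of 0.5, and the current primary test does not include that adjustment.

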#### 2.4.2. Secondary outcome

The secondary outcomes include the ISI (31, 32) and Epworth Sleepiness Scale (ESS) (33, 34) to assess the severity of insomnia and daytime sleepiness, respectively. The ISI and ESS will be measured at baseline, 2 weeks (during treatment), and 4 weeks (post-treatment). Polysomnography (PSG) will be performed at baseline and at 4 weeks (post-treatment) for one night, and the total sleep time (TST), sleep efficiency (SE), sleep onset latency (SOL), and wake-up after sleep onset (WASO) will be assessed. The participants will be instructed to keep a sleep diary during the study period. The TST, SE, SOL, and WASO for 7 days will be extracted from the sleep diary at baseline, 2 weeks, and 4 weeks. Blood biomarkers of cortisol, C-reactive protein, and adiponectin will be measured at baseline and at 4 weeks to assess the stress levels and inflammatory markers. The participant timeline is shown in Figure 1.

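### The safety set and the FA set both ask for more than one where at least one is needed, so single-dose participants leave the main safety analysis and FA membership turns on an undefined term

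*Protocol article*

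**What the plan says.** Section 2.11.1 sets three populations. The main efficacy population "is the Per Protocol (PP) set, and Full Analysis (FA) set will be used supplementary". The FA set takes in "participants who are randomized into groups and who complete more than one assessment after the administration of the investigational products". The main safety population is "the safety set, which includes participants administered the investigational products more than once". The same section adds that "missing data in the FA set will be imputed using the last observation carried forward method".

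Section 2.4.2 gives the timing of the secondary outcomes. For the Insomnia Severity Index (ISI) and Epworth Sleepiness Scale (ESS) there are two post-dose times, 2 and 4 weeks. The diary variables "will be extracted from the sleep diary at baseline, 2 weeks, and 4 weeks". "Polysomnography (PSG) will be performed at baseline and at 4 weeks (post-treatment) for one night", so polysomnography has one post-dose time. For the primary outcome, the Pittsburgh Sleep Quality Index (PSQI), section 2.4.1 states only the value after 4 weeks. The Figure 1 schedule is not visible in the text available for this review.

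Section 2.3 makes one administration a single bedtime intake of four capsules. Section 2.13 has adverse events collected at every visit.

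**The concern.** Both rules set the threshold one step higher than their purpose requires. A safety population exists to count everyone exposed. A rule that starts at the second dose drops those who took the product once and stopped, a group that may include people who stopped because of an acute reaction. The article describes this as the first human study of the extract's effect on sleep (section 3), plans no data monitoring committee or interim analysis (section 2.12), and will submit the safety results to the Korean regulator (section 4.4). The final safety table therefore carries most of the weight.

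The FA set is the only planned efficacy population beside the per-protocol (PP) set, so it is where a reader would look to see whether dropout drives the PP result. If it can shrink to the completers, it cannot serve that purpose. Because the article does not say whether an assessment is a visit, an instrument or a PSQI score, the written rule does not settle who belongs.

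**Working it through.** **Planned numbers.** Section 2.5 gives a difference of 2.50, SD 3.4, 5% significance, 80% power, 25% dropout and 40 per group. With a two-sided test (sidedness is not stated), n = 2 × [3.4 × (1.960 + 0.842) / 2.50]² = 29.03, rounded up to 30 per group. Then 30 / (1 − 0.25) = 40. The plan's figure reproduces and the sample size is not in question. It implies 60 completers and 20 dropouts among 80.

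**Safety set.** One intake is one administration, so a participant who stops after the first dose fails the rule "which includes participants administered the investigational products more than once". If an arm of 40 has k participants with an event and one of them is such a case, the omission changes the rate from k/40 to (k − 1)/39:

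- k = 1: 1/40 − 0/39 = 2.5 percentage points.
- k = 5: 5/40 − 4/39 = 12.5% − 10.3% = 2.2 percentage points.

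The documents do not say how often a participant would stop after one dose. With an assumed proportion p, the expected number left out per arm is 40p, and the chance of at least one is 1 − (1 − p)⁴⁰:

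| Assumed p | Expected left out per arm | Chance of at least one |
|---|---|---|
| 1% | 0.4 | 33% |
| 2% | 0.8 | 55% |
| 5% | 2.0 | 87% |

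**FA set, by meaning of assessment.**

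- *Visit.* The text gives two post-dose times, weeks 2 and 4. More than one means both, so FA = 60, the completers. Under an at-least-one rule, FA = 60 + 20f, where f is the share of dropouts who leave after the week-2 visit. The documents do not give f. For f = 0, 0.25, 0.5, 0.75 and 1, FA = 60, 65, 70, 75 and 80. The wording therefore costs 0 to 20 participants. It also leaves last observation carried forward (LOCF) almost nobody to apply to, because members would have attended both visits.
- *Instrument.* ISI and ESS at week 2 are already two assessments. A participant who leaves after week 2 is in the FA set, which is about the size it would have under the at-least-one rule.
- *PSQI score.* The text states one post-dose PSQI, at week 4. On that text alone nobody could have more than one. The missing Figure 1 might show another, so this reading is noted and not relied on.

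**The case against.** The best defence is that both phrases are slips for at least one. The LOCF rule in the same section supports this for the FA set: it presupposes members without a week-4 value, and the visit reading removes nearly all of them. Section 4.3 also provides a blind review to confirm the analysis set before lock. The intention is probably as the defence says, but nothing in the article restates either rule, and that review would start from the written criteria.

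A reader might infer that the FA set is, as written, a near-completer set. The documents do not support that without the visit reading, and the instrument reading is at least as natural given the week-2 schedule. Nor do they support attributing all 20 dropouts to the wording. That is a ceiling even on the visit reading, because participants who leave before week 2 would fail an at-least-one rule too.

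A reader might also infer that anyone harmed by the first dose vanishes from safety. That goes too far: a participant who takes a second dose stays in the set, and the event of one who does not is still collected under section 2.13. What is lost is membership of the main safety set.

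Finally, the FA set is only supplementary to PP, so the effect on the primary efficacy conclusion is limited. That stands.

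**Conclusion.** The safety-set rule is wrong as written: it excludes anyone who stops after a single dose, and no reading of assessment bears on that. Few participants are likely to be affected, but one omitted case changes an arm's event rate by about 2.5 percentage points when it is the only event, and slightly less when there are others. The chances of an omission shown above rest on assumed stopping rates.

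The FA rule is badly fixed, but not shown to be harmful on every reading. By visit it gives 60 of 80 at the planned dropout, against 60 to 80 under an at-least-one rule, with the timing of dropout unstated. By instrument the difference is about nil. The safety wording is the more serious part; the FA wording is a supporting point of clarity.

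**What to change.** In section 2.11.1, define the safety set as all participants who took at least one dose. Define the FA set as randomised participants with at least one post-dose efficacy assessment, analysed in the assigned arm, and state whether an assessment is a visit, an instrument or a PSQI score.

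The cost is two phrases changed before database lock, with no new data. Section 4.1 requires approval of amendments by both review boards before they are applied. The change should be in place before the blind review of the analysis sets, so that membership is not settled by reinterpretation at that stage. An FA set of all randomised participants would be a larger design change, which this wording error does not by itself require.

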#### 2.11.2. Statistical method for analyzing primary and secondary outcomes

The change from the baseline PSQI global score at 4 weeks between the two groups will be compared using a two-sample *t*-test or Wilcoxon rank sum test, according to the normality of data. Additionally, changes in the PSQI global score over time in each group will be compared using a paired *t*-test. A generalized linear model (GLM) with covariates of caffeine consumption, age, body mass index, smartphone usage time, and drinking habits can also be conducted. In case of significant differences in baseline characteristics between the two groups, these baseline characteristics can be considered as covariates in conducting the GLM.

The statistical method used for analyzing secondary outcomes is identical to that used to analyze the primary outcome.

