## 2. Methods and analysis

### 2.1. Study setting

This clinical trial will be conducted in two academic university hospitals in Korea, one in Seoul and the other in Daegu.

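### The primary test uses unadjusted PSQI change scores and leaves out baseline PSQI; this is valid but imprecise, and its stated 80% power rests on an unstated baseline to week-4 correlation

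*Protocol article*

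**What the plan says.** Section 2.11.2 defines the primary comparison in these words: "The change from the baseline PSQI global score at 4 weeks between the two groups will be compared using". The method it names is either a t-test for independent samples or a rank sum test, depending on whether the data look normal. Neither test adjusts for anything. A generalized linear model is permitted but not required, with "covariates of caffeine consumption, age, body mass index, smartphone usage time, and drinking habits". Baseline PSQI is not on that list, and neither is site. Other baseline characteristics may enter the model only if they differ significantly between the groups. The secondary outcomes are to be analysed in the same way.

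Section 2.5 sizes the trial for a difference in change from baseline. On the variability it says: "the largest value of the standard deviation of the PSQI global score was 3.4", and it acknowledges that the source trial gave no SD of change. It then proceeds as follows: "the mean difference and pooled standard deviation were estimated as −2.50 and 3.4, respectively". From these values, a significance level of 5%, power of 80% and an allowance of 25% for dropout, it arrives at 40 per group. No correlation between baseline and week-4 PSQI is given.

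**The concern.** Baseline PSQI is recorded for every participant, because it determines eligibility (section 2.2.1) and is needed to form the primary outcome (section 2.4.1). It is the obvious covariate for week-4 PSQI, yet neither the primary test nor the named covariate list uses it. Subtracting the baseline fixes its coefficient at 1. ANCOVA estimates that coefficient, and with equal SDs at the two visits it equals the correlation. Whenever the correlation is below 1, the change score therefore carries avoidable noise.

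This affects the sample size as well. The SD of a score and the SD of a change are different quantities, linked by the correlation. Using 3.4 for the change amounts to an assumption about that correlation which the article does not make openly. If the assumption fails, a small trial runs below its stated power, and section 3 itself says that a large effect may not be obtained.

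**Working it through.** **Inputs.** From section 2.5: difference 2.50, SD 3.4, 5% level, 80% power, 25% dropout, 40 per group. Evaluable per group: 40 × 0.75 = 30. A two-sided test is assumed, because it reproduces 40 (a one-sided test would give 31). The correlation ρ between baseline and week-4 PSQI is not in the document, so it is an assumption shown as a range.

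**Step 1: the plan's own figure.** n = 2 × (1.96 + 0.8416)² × (3.4/2.5)² = 29.03, rounded up to 30. Then 30/0.75 = 40. The stated size is reproduced, so 3.4 was used as the SD of change. Exact t-test power at 30 per group is 79.97%.

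**Step 2: what 3.4 implies.** With SDs b at baseline and w at week 4, the SD of change is √(b² + w² − 2ρbw). Setting it equal to 3.4 gives the smallest ρ that supports the plan: ρ = (b² + w² − 3.4²)/(2bw). The SDs other than 3.4 are assumptions.

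| SD at baseline / week 4 | Smallest ρ | Change-score power at ρ = 0.3 |
|---|---|---|
| 3.4 / 3.4 | 0.50 | 66% |
| 3.0 / 3.0 | 0.36 | 76.5% |
| 2.5 / 3.4 | 0.37 | 76% |
| 2.5 / 2.5 | 0.08 | 90% |

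**Step 3: change score against ANCOVA.** Take SD 3.4 at both visits and 30 per arm. The SD of change is 3.4√(2(1 − ρ)), and the ANCOVA residual SD is 3.4√(1 − ρ²). The ratio of the two variances is (1 − ρ²)/(2(1 − ρ)) = (1 + ρ)/2. Power is from the noncentral t distribution.

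| ρ | SD of change | Power, change score | ANCOVA residual SD | Power, ANCOVA | Variance ratio |
|---|---|---|---|---|---|
| 0.3 | 4.02 | 66% | 3.24 | 83.5% | 0.65 |
| 0.4 | 3.72 | 73% (72.5%) | 3.12 | 86% | 0.70 |
| 0.5 | 3.40 | 80% | 2.94 | 90% | 0.75 |
| 0.6 | 3.04 | 88% | 2.72 | 94% | 0.80 |

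Charging ANCOVA one or two further degrees of freedom lowers these powers by no more than about 0.1 percentage point.

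**Step 4: how far ANCOVA protects the power.** Its residual SD is w√(1 − ρ²), which never exceeds w. If w is at most 3.4, power is at least about 80% for any ρ. If w were 4.0 and ρ = 0.3, the residual SD would be 4.0 × √0.91 = 3.82 and power about 70%.

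**The case against.** Several points on the other side stand.

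- **The 0.5 threshold is conditional.** It needs an SD of 3.4 at both visits, and section 2.5 presents 3.4 as the largest SD reported. It may be conservative, and step 2 shows that smaller SDs relax the requirement considerably. A reader might infer that the trial is underpowered. The document does not support that, because it gives neither the correlation nor the SDs to expect in this sample.
- **The entry criteria do not settle the matter.** It is tempting to argue that they narrow the baseline range and so lower the correlation. They would also shrink the baseline SD, which works the other way. The net direction is not shown.
- **The test is valid.** A reader might infer that the change-score test is biased by regression to the mean. Under randomisation it is unbiased with the correct type I error. An estimate shifts only conditionally on a chance imbalance: with ρ = 0.5, a 1-point baseline imbalance moves it by about 0.5 points. The standard error of that imbalance at 40 per arm is 3.4 × √(2/40) = 0.76, so 1 point is a 1.3 standard error event, and about 81% of trials would show less.
- **Site.** Two hospitals take part, but the article gives no site variance and does not mention stratification by site. No loss of precision from omitting site can be demonstrated.
- **The plan is partly open about this.** Section 2.5 admits that the SD of change was unavailable, and it reduced the source trial's difference from 3.95 to 2.50, which is a real margin on the effect.

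The clause on significant imbalance answers less than it seems to. It could admit baseline PSQI, but only at the analyst's option, after looking at the data, and outside the primary test.

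**Conclusion.** The point stands as an avoidable loss of precision together with an unsupported power input. It is not an error of validity. If the SDs at the two visits are equal, ANCOVA on baseline PSQI has (1 + ρ)/2 of the variance of the change score: 35% lower at ρ = 0.3 and 25% lower at ρ = 0.5. The arithmetic behind 40 per group is correct, but the 80% applies to the planned test only if the correlation reaches a value that the article does not state and that itself depends on the SDs.

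It would go too far to say that ANCOVA guarantees 80%. It removes the dependence on the correlation, but it still relies on a week-4 SD of at most 3.4. The power figures rest on that borrowed SD, on 30 evaluable per arm and on an assumed range for ρ. The change is worth making before unblinding.

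**What to change.** **Section 2.11.2.**
- Make the primary analysis a prespecified ANCOVA of week-4 PSQI (or change in PSQI) on treatment and baseline PSQI, reporting the adjusted mean difference with its 95% confidence interval.
- Use the same form for the secondary outcomes, each with its own baseline value.
- Delete the rule that admits covariates when baseline differences are significant.
- Site may be added as a covariate, although its gain cannot be quantified from the document.

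**Section 2.5.** State that 3.4 is an SD of the PSQI score, and that it bounds the ANCOVA residual SD for any correlation provided the week-4 SD does not exceed 3.4. The sample size of 40 per group can then stay as it is.

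**Cost.** Wording in two sections, one or two degrees of freedom and a linear-model assumption. No new data or participants are needed.
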